### Objectives

The primary objective for the CDCS is to determine the prevalence of VC in Chinese patients with CKD on HD or PD. The secondary objectives are:To test the hypothesis that a greater severity of baseline VC is associated with a higher risk for all-cause and CVD mortality, and non-fatal CV events in Chinese patients with CKD on HD or PD.To investigate the association between all-cause and CVD mortality, and non-fatal CV events and disease management (using serum levels of calcium, phosphorus and intact parathyroid hormone (iPTH), fibroblast growth factor 23 (FGF23) and related medications) in Chinese patients with CKD on HD or PD.To investigate the impact of current disease management on VC.To evaluate the control rate of patients achieving target goal of serum phosphorus, calcium and iPTH.To validate the cardiovascular calcification index (CCI) in Chinese patients with CKD on HD or PD.

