### Data collection

Visit 1 is at baseline/study entry and the follow-up includes 4 visits at 6 ± 1 month, 12 ± 1 month, 18 ± 1 months and 24 ± 1 month, respectively. The flow chart of detailed data and sample collection can be found in Table 3. At baseline, eligible patients will be evaluated for demographic information, smoking, alcohol drinking status, biochemical data, dialysis variables, concomitant medications, and personal and family disease history. Physical measurements including weight, height, body mass index (BMI) and vital signs (blood pressure and heart rate) will be obtained. Older age (male >55 years, female >65 years), arterial hypertension, family history (mother, father, brother, sister, children) of premature cardiovascular disease (≤55 years male, ≤65 years female), smoking, impaired glucose tolerance and/or impaired fasting glucose, dyslipidemia, and obesity are considered potent cardiovascular risk factors. The baseline biochemical data will be obtained using local routine laboratory methods performed within a week at the start of the study. If laboratory tests of serum 25-hydroxyvitamin D (25-OH Vit D) and FGF23 cannot be conducted in some centers, blood samples for testing 25-OH Vit D and FGF23 will be sent by the site study staff to those centers that can perform the assay. Blood sample collection will be performed according to the laboratory manual. Results from routine samples defined as samples taken within a week at the visit. Serum phosphorus, total calcium and iPTH will be tested at each visit. Target level of serum phosphorus, total calcium and iPTH in CKD stage 5 are defined according to Kidney Disease Outcomes Quality Initiative (K/DOQI) and KDIGO guidelines, respectively (Table 4) [20, 21]. Total serum calcium is adjusted if serum albumin is <4g/dL to better reflect the free calcium, using the formula proposed by the US Bone Metabolism Association: corrected total calcium (mg/dL) = total calcium (mg/dL) + 0.8 × [4.0 − serum albumin (g/dL)]. Date, time, primary reason and characteristics of death with autopsy results if applicable and any supportive documents that relate to fatal and nonfatal CV events are defined as clinical outcomes, and will be collected during the follow-up.

**Table 3 Tab3:** Study flow chart of the CDCS

Procedures	Visit time (month)				
	Baseline	6 ± 1	12 ± 1	18 ± 1	24 ± 1
Data release consent form	●				
Demography data	●				
Inclusion/exclusion criteria	●				

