Physical measurements (vital signs)	●				
Smoking and alcohol drink status	●				
Cardiovascular risk factors	●				
Disease history	●				
Concomitant medications	●	●	●	●	●
Hemoglobin, hematocrit	●				
Serum total calcium, phosphorus, iPTH	●	●	●	●	●
25-OH Vit D, FGF23	●		●		●
Glucose, HDL-C, LDL-C, TC and TG	●				
hs-CRP	●				
Serum albumin, ferritin, alkaline phosphatase	●				
Urea, uric acid, creatinine	●				
ABI	●				
Kt/V, dialysate calcium concentration	●				
Dialysis vintage, dialysis frequency and modality, membrane type	●				
EBCT or MDCT scan	●				●
Plain lateral lumbar radiograph	●				●
Echocardiography, LVMI/LVH	●				●
Clinical outcomes		●	●	●	●

*iPTH* Intact parathyroid hormone, *25-OH Vit D* serum 25-hydroxyvitamin D, *FGF23* Fibroblast growth factor 23, *HDL-C* High density lipoprotein-cholesterol, *LDL-C* Low density lipoprotein-cholesterol, *TC* Total Cholesterol, *TG* Triglyceride, *hs-CRP* High-sensitivity C-reactive protein, *ABI* Ankle-brachial index, *EBCT* Electron beam computed tomography, *MDCT* Multi-detector computed tomography, *LVMI* Left ventricular mass index, *LVH* Left ventricular hypertrophy

**Table 4 Tab4:** Target level of serum phosphorus, calcium and iPTH in CKD stage 5

Biochemical parameters	K/DOQI	KDIGO
Serum phosphorus	3.5–5.5 mg/dL (1.13–1.78 mmol/L)	Toward Normal [2.5–4.5 mg/dL (0.81–1.45 mmol/L)]
Corrected total calcium	8.4–9.5 mg/dL (2.10–2.38 mmol/L)	Maintain Normal [Healthy: 8.5–10.5 mg/dL (2.13–2.63 mmol/L)]
Serum iPTH	150–300 pg/mL (16.5–33.0 pmmol/L)	2–9 times the upper normal limit (65 pg/mL, 6.9 pmmol/L)

*K/DOQI* Kidney Disease Outcomes Quality Initiative, *KDGIO* Kidney Disease: Improving Global Outcomes, *iPTH* Intact parathyroid hormone

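### The iPTH row of Table 4 uses two different pg/mL-to-pmol/L conversions, so one of the two guideline targets (not both) has different limits depending on the unit.

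*Protocol article*

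**What the plan says.** Under Objectives, one secondary aim is "To evaluate the control rate of patients achieving target goal of serum phosphorus, calcium and iPTH". Under Data collection, the article states "Target level of serum phosphorus, total calcium and iPTH in CKD stage 5 are defined according to Kidney Disease Outcomes Quality Initiative (K/DOQI) and KDIGO" and points to Table 4 for the limits. In the iPTH row the K/DOQI cell reads "150–300 pg/mL (16.5–33.0 pmmol/L"), and the KDIGO cell reads "2–9 times the upper normal limit (65 pg/mL, 6.9 pmmol/L"). The printed unit pmmol/L is evidently a misprint for pmol/L and plays no part in this point.

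On how the values arise, the same section says "The baseline biochemical data will be obtained using local routine laboratory methods performed within a week at the start of the study" and "Serum phosphorus, total calcium and iPTH will be tested at each visit". Table 3 confirms iPTH at all five visits. The article names neither a common reporting unit for iPTH nor a conversion factor.

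**The concern.** A mass-to-molar conversion for one analyte needs one factor, so all the paired limits in the iPTH row should agree on it. They do not. Table 4 is the definition that sorts patients into at target or not at target for a stated secondary objective, and the sorting is repeated at each visit. If the pg/mL limits and the pmol/L limits are different rules, a sample close to a limit can be classified differently according to the unit in which it was reported. At stake is the iPTH control rate for one of the two guidelines, and its comparability between centres if centres report in different units.

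**Working it through.** **Inputs.** All limits are from Table 4: K/DOQI 150 ↔ 16.5 and 300 ↔ 33.0; KDIGO upper normal limit 65 ↔ 6.9, with multiples 2 and 9. The planned number of patients, 1520, is from Study design.

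**Step 1: implied factors.** Factor = pmol/L ÷ pg/mL. The printed pmol/L values carry one decimal, so the rounding interval is (value ± 0.05) ÷ pg/mL.

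| Pair | Factor | Interval allowing for rounding |
|---|---|---|
| 16.5 / 150 | 0.1100 | 0.1097–0.1103 |
| 33.0 / 300 | 0.1100 | 0.1098–0.1102 |
| 6.9 / 65 | 0.1062 | 0.1054–0.1069 |

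The third interval does not meet the other two, so no single factor reproduces the row. The ratio is 0.1100 / 0.10615 = 1.036, a difference of 3.6 %.

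**Step 2: the other rows as a check.** Done the same way with ± 0.005, the four phosphorus pairs share a common factor (0.3227–0.3233), and so do the four calcium pairs (0.2500–0.2506). Only the iPTH row fails.

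**Step 3: what each factor does to each column.**

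- At 0.1062 (6.9/65):
  - K/DOQI in pmol/L converts back to 16.5 / 0.10615 = 155.4 and 33.0 / 0.10615 = 310.9 pg/mL, against the printed 150 and 300.
  - Allowing for rounding of 6.9, the lower limit is 154.3–156.6 and the upper limit 308.6–313.1.
  - KDIGO is consistent: 2 × 6.9 = 13.8 and 9 × 6.9 = 62.1 pmol/L give 130 and 585 pg/mL.
- At 0.1100:
  - K/DOQI is exact at both limits.
  - KDIGO in pmol/L converts back to 13.8 / 0.1100 = 125.5 and 62.1 / 0.1100 = 564.5 pg/mL, against 2 × 65 = 130 and 9 × 65 = 585.

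Examples at 0.1062: 152 pg/mL is inside the K/DOQI range, but it equals 16.1 pmol/L, below 16.5. A value of 305 pg/mL is outside, but it equals 32.4 pmol/L, below 33.0 and so inside.

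**Step 4: how many patients could change class.** The article gives no iPTH distribution. Assume log-normal iPTH with median m of 200–350 pg/mL and log SD s of 0.7–1.0, and assume every result is in pmol/L and judged by the printed pmol/L limits. With F(x) = Φ[(ln x − ln m)/s]:

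- K/DOQI at 0.1062: lost = F(155.4) − F(150); gained = F(310.9) − F(300).
  - m = 200, s = 0.7: 1.88 % lost, 1.69 % gained; 3.6 % change class (about 54 of 1520), net −0.2 points.
  - m = 350, s = 1.0: 1.01 % lost, 1.41 % gained; 2.4 % change class (about 37 of 1520), net +0.4 points.
  - Across the whole range: 2.4–3.6 % change class, net −0.2 to +1.0 points.
- KDIGO at 0.1100: gained = F(130) − F(125.5); lost = F(585) − F(564.5).
  - Across the range, 2.1–2.3 % change class.
- K/DOQI at 0.1100 and KDIGO at 0.1062: none.

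**The case against.** The case for leaving this alone has five parts.

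- **Misclassification is conditional.** Some centres must report in pmol/L, and units must not be harmonised before classification. The article states neither. This stands: if all results are in pg/mL, the table is wrong but no patient is misclassified.
- **Unit handling belongs elsewhere.** It is commonly left to a laboratory manual (the article mentions one), a data-management plan or an SAP. This also stands, and the absence of a stated reporting unit is not the finding. The finding is that figures printed in this document disagree. A later handling rule could prevent harm but would not make the two cells agree.
- **The columns are separate rules.** They come from separate guidelines, and the 65 and 6.9 might be reference limits quoted in each unit rather than a conversion. That is possible. Even so, the KDIGO column would then give one range in pg/mL and a different one in pmol/L if 0.1100 is the conversion.
- **The size is small.** The 95 % interval around a control rate of 30–40 % in 1520 patients is about ±2.4 points, wider than the largest net K/DOQI shift. With half the results in pmol/L, the number changing class also halves.
- **No inferential result depends on it.** Secondary analysis describes models using serum iPTH level, not target attainment. This stands.

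A reader might infer that both the K/DOQI and the KDIGO control rates are distorted, or that centres will in fact apply different limits. The document supports neither. Under either of the two factors it contains, only one column conflicts, and it does not say that any centre reports in pmol/L.

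**Conclusion.** Wrong as written, and minor. The iPTH limits in Table 4 cannot all be equivalent across units, and this follows from the printed figures alone. Whichever of the two implied factors holds, exactly one guideline column has limits that depend on the unit: K/DOQI at 0.1062, KDIGO at 0.1100.

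The effect on patients is an upper bound under stated assumptions: all results in pmol/L, printed limits applied in the reported unit, and log-normal iPTH over the range above. About 2–4 % would then change status for that one guideline. For K/DOQI the net change in the control rate is about 1 percentage point or less, because gains and losses partly cancel. The reach is one descriptive secondary rate. The primary prevalence analysis, the sample size and the Cox models do not use these limits.

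**What to change.** Reconcile the two iPTH cells of Table 4 to one conversion factor. State that target attainment is classified in one analysis unit, using only that unit's limits, with results reported in the other unit converted by the same factor first. The document does not show which of the printed limits is right, so the sponsor should settle that against the guidelines it cites. The cost is one corrected table row and one data-standardisation step, with no extra burden on patients or sites.

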### Imaging methods

VC images will be taken within a week of enrolment and the final visit of the study. Coronary artery calcification (CAC), abdominal aortic calcification (AAC) and cardiac valve calcification will be assessed by electron beam computed tomography (EBCT) or multi-detector computed tomography (MDCT), plain lateral lumbar radiograph and echocardiography, respectively. In addition, results of left ventricular mass index (LVMI) and left ventricular hypertrophy (LVH) through echocardiography will be taken within a week of enrolment and the final visit of the study as well.

CAC is measured by EBCT or MDCT as originally described by Agatston et al. [22]. Thirty to forty contiguous tomographic slices will be obtained at 3-mm intervals beginning 1 cm below the carina and progressing caudally to include the entire coronary tree. An attenuation threshold of 130 Hounsfield units (HU) and a minimum of 3 contiguous pixels will be used for identification of a calcific lesion. The density factor is assigned in the following manner: 1 for lesions with peak attenuation of 130–199 HU, 2 for lesions with peak attenuation of 200–299 HU, 3 for lesions with peak attenuation of 300–399 HU, and 4 for lesions with peak attenuation >400 HU [22]. Total CACS is determined by summing individual lesion scores from each of four anatomic sites (left main, left anterior descending, left circumflex, and right coronary artery). The CACS will be divided into approximate tertiles (0, <100, ≥100, ≥400 and ≥1000). CAC progression is evaluated as a continuous variable by calculating the difference in Agatston score between the two CT scans divided by the time between imaging. The 2-year progression of CAC is categorized as follows: absent (≤25th percentile), moderate (25th-75th percentiles), and accelerated (≥75th percentile).

AAC is assessed by semiquantitative scoring of a plain lateral lumbar radiograph using previously validated 24-point aortic calcification scale as originally described by Kauppila et al. [23]. Midpoint of the intervertebral space above and below the vertebrae will be used to assess calcific deposits in the aorta adjacent to each lumbar vertebra (L1-L4), and lesion grading is based on a 0–3 scale: 0, no aortic calcific deposits; 1, small scattered calcific deposits (<1/3 of the longitudinal wall of the aorta); 2, calcific deposits ≥1/3 and <2/3; 3, calcific deposits ≥2/3 [23]. The scores, obtained separately for the anterior and posterior wall, result in a range from 0 to 6 for each vertebral level and 0 to 24 for the total AAC score. The AAC will be divided into approximate tertiles (0, <5, and ≥5, ≥16).

Cardiac valve calcification is measured by a standard two-dimensional M-mode color Doppler echocardiography. Cardiac valve calcification will be considered present when bright echoes of more than 1-mm thickness are seen on 1 or more cusps of the aortic valve, mitral valve, or mitral annulus. Thereafter, patients are divided into 3 groups according to number of calcified valves: patients without valve calcification, patients with a single (aortic or mitral) valve calcification, and patients with calcifications in both valves.

LVMI is calculated with echocardiography and normalized to body height as an index in g/m^2^. LVH is diagnosed when LVMI is >125 g/m^2^ in males or >120 g/m^2^ in females.

### CCI

Points of CCI are assigned for patients age (60–69 and 70 years, 1 and 2 points, respectively), dialysis vintage 2 years (1 point), aortic and mitral valve calcification (3 and 1 points, respectively), and abdominal aorta X-ray scores of 1–6 and 7 (2 and 4 points, respectively). Race, sex and pulse pressure do not contribute to the CCI. Therefore, the CCI ranges from 0 to 11 points.

### Demographic and baseline data analysis

Categorical data will be presented in contingency tables along with frequencies and percentages. Continuous data will be summarized with frequency (n), mean, standard deviation, median, 1st quartile, 3rd quartile, minimum and maximum. Descriptive analyses will be presented by groups (with VC vs. without VC, with CAC vs. without VC, with AAC vs. without VC, with cardiac valve calcification vs. without VC). For categorical variables, group comparison will be based upon the results of the Chi-square test (for 2 × 2 tables) or the Cochran-Mantel-Haenszel test (for r × c tables, where r or c is greater than 2). Chi-square test will be replaced by Fisher’s exact test if the expected frequency in any of the cells of the contingency table is less than 5. For continuous variables, group comparison will be based upon the results of the *t*-test or the Wilcoxon rank-sum test, depending on the distribution.

### Primary analysis

Prevalence of VC at baseline and its corresponding 95 % confidence interval (CI) will be presented. Prevalence of CAC, AAC and cardiac valve calcification at baseline and their corresponding 95 % CIs will also be presented.

### Secondary analysis

The key secondary analysis will be a comparison of survival (based on all-cause mortality) between patients with and without VC based upon the log-rank test performed at a significance level of 0.05. Hazard ratios and 95 % CIs will be calculated by a Cox proportional hazard regression model. In addition, the multivariable Cox proportional hazard regression model will be performed, using the stepwise method (*p* <0.05 as the inclusion criteria and *p* <0.10 as the exclusion criteria), considering with or without VC as the independent variable and the baseline variables with *p* <0.25 in univariate analysis as covariates, and hazard ratios and 95 % CIs for each factor will be presented. The same analyses will also be done for survival (based on CVD mortality) and non-fatal CV event free survival. For each of the above endpoints, the separate comparisons of patients with CAC, with AAC, with cardiac valve calcification to patients without VC will be made at a significance level of 0.05.

Association between disease management (including serum level of calcium, phosphorus and iPTH, and medications), 25-OH Vit D, FGF23, and all-cause/CVD mortality, non-fatal CV events will be identified with Cox proportional hazard regression model, considering disease management as the independent variables. Associations will be tested using the Wald test and described through the hazard ratios and 95 % CIs.

Association between disease management, 25-OH Vit D, FGF23, ankle-brachial index (ABI), and LVMI/LVH and the occurrence of CAC, AAC and cardiac valve calcification at baseline will be identified with the logistic regression model. The univariate logistic regression model will be performed separately, considering disease management, ABI, and LVMI/LVH as independent variables. Associations will be tested using the Wald test and described through the odds ratios and 95 % CIs.

Association between disease management, 25-OH Vit D, FGF23, ABI, and LVMI/LVH and severities (scores) of CAC, AAC and cardiac valve calcification at baseline will be identified with the linear regression model, considering disease management, ABI, and LVMI/LVH as independent variables.

Association between CAC progression and disease management, 25-OH Vit D, FGF23, ABI, as well as LVMI/LVH will be evaluated by ANCOVA as continuous variables and evaluated by ordinal multinomial logistic regression as categorical variables.

Receiver operating characteristic curve (ROC curve) will be performed to assess the ability of the CCI to predict the presence of CAC (lesion score ≥100, ≥400 or ≥1000), with the area under the curve (AUC), positive and negative likelihood ratios calculated.

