## Abstract

**Background:**

Vascular calcification is a common complication associated with chronic kidney disease and the major cause of cardiovascular disease in patients with end-stage renal disease. The vascular calcification risk burden is still unknown in China. This study aims to investigate the prevalence of vascular calcification and assess the predictive value of vascular calcification in patients with stage 5 chronic kidney disease on dialysis in China.

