MBD management is not optimized for Chinese dialysis patients and hyperphosphatemia is an important issue needing greater awareness [18]. However, there is limited knowledge about the impact of VC on Chinese dialysis patients in current disease management and dialysis patterns. Additionally, the VC risk burden is still unknown in China, causing poorer prognosis and inadequate dialysis management. The China Dialysis Calcification Study (CDCS) is the first large, prospective, multicenter, observational cohort study to investigate the prevalence of VC using different non-invasive imaging techniques and to assess the predictive value of VC with associated risk factors for all-cause and CVD mortality in dialysis patients with CKD stage 5D in China.

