## Discussion

VC is a major contributor to CVD, which is a significant cause of mortality in ESRD. However, the burden and management of VC in Chinese patients with CKD on dialysis are still unknown. Given that clinical trials are considered the best way to provide evidence and related knowledge for guidance, it is necessary to design a high quality national observational study that is capable of addressing these issues.

The CDCS is a uniquely-designed observational cohort study seeking to collect detailed clinical, biochemical and laboratory data to inform the prevalence and impact of management of VC in Chinese patients with CKD on dialysis, and test the hypothesis that baseline VC is a predictor for all-cause/CVD mortality and non-fatal CV events. This study aimed to recruit well-characterized patients in order to avoid incidence-prevalence bias, and the sample size will be large enough to achieve multiple study objectives with adequate variability [25].

This study may be limited by the nature of the design as an observational study, in comparison with randomized controlled trials which can commonly provide stronger evidence in the efficacy of therapies. Since the proportion of patients receiving HD or PD cannot be predefined, the strength of comparing the outcome between the two groups may be weakened. In addition, collection of some prognostic factors (e.g., brain natriuretic peptide and troponin) for CVD was not included in the study design as these tests will not be applicable for every enrolled patient in the real-world clinical practice setting.

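### The article announces the predictive value of VC for mortality, but its mortality analyses address association only, by presence or absence of calcification, and never use the graded scores

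*Protocol article*

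**What the plan says.** The aim is worded in two ways.

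- **Prediction.** The Abstract (Background) says the study will "assess the predictive value of vascular calcification in patients with stage 5 chronic kidney disease on dialysis in China". The Background section names the outcomes: "to assess the predictive value of VC with associated risk factors for all-cause and CVD mortality in dialysis patients". The Discussion says the study will "test the hypothesis that baseline VC is a predictor for all-cause/CVD mortality and non-fatal CV events".
- **Association.** The Methods/Design part of the Abstract speaks of an association between VC and mortality and non-fatal events. The first secondary objective is the hypothesis that "a greater severity of baseline VC is associated with a higher risk for all-cause and CVD mortality".

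For VC and death, the Secondary analysis section fixes the following:

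- The key secondary analysis "will be a comparison of survival (based on all-cause mortality) between patients with and without VC based upon the log-rank test".
- Hazard ratios and their 95 % "CIs will be calculated by a Cox proportional hazard regression model".
- A stepwise multivariable Cox model takes VC as a yes/no variable, with baseline covariates screened by univariate p-value.
- The same analyses are repeated for CVD mortality and for survival free of non-fatal CV events.
- Patients with CAC, with AAC and with valve calcification are each compared with patients without VC.

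The only ROC analysis closes that section. It "will be performed to assess the ability of the CCI to predict the presence of CAC" and includes the AUC and likelihood ratios. It does not concern death.

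**The concern.** A hazard ratio different from 1 shows that VC and death are associated. It does not show how well VC identifies the patients who will die, or how much it improves on age, dialysis vintage and disease history, which are known without imaging. An aim worded as predictive value invites both questions. The article uses discrimination measures where it asks whether the CCI predicts CAC, but names none for VC and mortality.

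The second gap is severity. The objective asks whether more severe VC carries higher risk. The Imaging methods section defines graded CAC and AAC scores, yet the planned mortality comparisons use only presence or absence. The scores appear as outcomes in regressions on disease management and as thresholds in the CCI analysis, and are not related to death.

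At stake is how the results are read. The Discussion ties them to clinical decisions, and a significant survival comparison is easily taken as evidence that VC is a useful predictor.

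**Working it through.** **Inputs** (Determination of sample size): 1520 patients, 1064 with VC and 456 without (7:3); 2-year survival 0.79 with VC and 0.86 without, so mortality 0.21 and 0.14; two-sided 0.05; 80 % power; 20 % loss to follow-up.

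**1. Reproduce the plan's figures.**

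- HR = ln(0.86)/ln(0.79) = 0.6398, as stated. Its inverse, VC against no VC, is 1.563.
- Freedman's log-rank formula with φ = 3/7: E = (1.960 + 0.842)² × (1 + φ·HR)² / [φ·(1 − HR)²] = 229.2 deaths.
- Mean 2-year mortality = 0.7 × 0.21 + 0.3 × 0.14 = 0.189.
- 229.2/0.189 = 1213 evaluable patients, and 1213/0.80 gives 1517 against the stated 1520.
- With 1520 × 0.80 = 1216 evaluable patients, Freedman power is 80.1 %.

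The sample size holds for the log-rank test.

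**2. Discrimination of VC yes/no for 2-year death at the same figures.**

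| | VC | No VC | Total |
|---|---|---|---|
| Deaths | 1064 × 0.21 = 223.4 | 456 × 0.14 = 63.8 | 287.3 |
| Survivors | 1064 × 0.79 = 840.6 | 456 × 0.86 = 392.2 | 1232.7 |

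- Sensitivity = 223.4/287.3 = 0.778.
- False-positive rate = 840.6/1232.7 = 0.682, so specificity = 0.318.
- AUC for a binary marker = (0.778 + 0.318)/2 = 0.548.
- LR+ = 0.778/0.682 = 1.14; LR− = 0.222/0.318 = 0.70.
- A Harrell-type C over 2 years (exponential survival, ties counted one half) is 0.543.

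**3. Sensitivity to assumptions.** The Background cites a VC prevalence of 80–99 % in dialysis patients. Holding the two mortality risks at 0.21 and 0.14 while prevalence changes is an assumption made here.

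| VC prevalence | 50 % | 60 % | 70 % | 80 % | 90 % | 99 % |
|---|---|---|---|---|---|---|
| AUC | 0.561 | 0.556 | 0.548 | 0.536 | 0.519 | 0.502 |

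If the hazard ratio were 3 (assumed), with 70 % VC and 18.9 % overall mortality, the AUC would be about 0.60.

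**4. Significance beside discrimination.** With no loss, 287 deaths are expected. The expected Schoenfeld z is √(287.28 × 0.7 × 0.3) × |ln 0.6398| = 3.47, p about 0.0005. At that same effect the AUC is 0.548, so a small p-value and weak discrimination can occur together.

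**The case against.** The strongest reply is that the formal objective and the Abstract's Methods ask about association, for which log-rank tests and Cox models are standard. Predictor is often used loosely for a prognostic factor in a regression model, and no sentence commits the study to measuring discrimination for death. The multivariable model bears on whether VC carries information beyond other baseline variables. A condensed article may also leave performance measures to an analysis plan that is not shown.

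Most of this stands. The planned tests are not wrong, and for VC presence they answer the association question. The absence of a C-index from a condensed article would not be a finding on its own. Two things remain. The article describes its aim in two ways that call for different analyses. It also fixes the mortality analysis in detail without the severity that its own objective names. An adjusted hazard ratio is still not a measure of added discrimination.

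A reader might infer that the plan will declare VC a predictor from p < 0.05 alone. The article states no such rule, and it requires hazard ratios with confidence intervals. A reader might also take 0.548 as the predictive ability of calcification in general. It describes one unadjusted yes/no marker at the planned effect, and the documents give no figures for graded scores or an adjusted model.

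**Conclusion.** The point holds as a mismatch between announced aim and planned analysis, and it is worth correcting. The Abstract's Background, the Background and the Discussion promise prediction of death. The Abstract's Methods and the Objectives promise association, in the Objectives with severity. The Secondary analysis section delivers association by presence or absence only.

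At the plan's own figures, VC yes/no has an AUC of about 0.55 for 2-year death, so a significant log-rank test would not by itself demonstrate useful prediction. This rests on the 7:3 split and the 21 % and 14 % mortality assumed for the sample size. It implies no error in the sample size, no invalid test and no unanswerable objective.

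**What to change.** In Secondary analysis, for all-cause and CVD mortality:

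1. Fit a Cox model with pre-specified baseline covariates that are already collected, for example age, sex, dialysis vintage and modality, with diabetes and prior CVD taken from the disease history.
2. Add VC to it and, in separate models, the CAC score and the AAC score.
3. Report the hazard ratios and the change in C-index or 24-month AUC with a bootstrap 95 % CI.
4. Describe the log-rank and hazard ratio results as association, and base any statement on predictive value on step 3.

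At minimum, reword the aim in the Abstract, Background and Discussion to match the Objectives. That alone would leave the severity hypothesis without a mortality analysis, which step 2 supplies.

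The cost is wording and some programming, with no new visits, imaging or patients. The drawback is that the reported predictive value may look modest.
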